#### Statistical Methods

##### General principles

The basic analysis method is the degree of change between the results of the baseline test performed before the clinical trial and the results of the test performed at the end of the clinical trial for the efficacy evaluation indicators, and the significance level is 0.05 by two-sided test.

For the efficacy portion of the study, all data from study participants will be analysed using both an intention-to-treat analysis (ITT), in which all participants who met the inclusion/exclusion criteria and who voluntarily agreed to participate in the human study and were randomized regardless of protocol violations or dropouts, and a per-protocol analysis (PP), in which all participants who were randomized will be included in the analysis, excluding participants with noncompliance or missing data. Missing observations for efficacy endpoints will be analysed using the last observation carried forward (LOCF) method, and missing observations for safety endpoints will be treated as missing.

As assigned analyses include all participants who have completed the baseline and final examinations, with the last examination data considered the final examination data. The safety analysis methodology will also follow the as assigned analysis methodology. As-treated analyses will include patients who completed the final examination with no major protocol violations.

The results of the two analyses should theoretically agree within the same study, but if there is an induced difference between the results, a plausible explanation for the difference should be provided.

For statistical analyses other than those specified in this protocol, please refer to the statistical guidelines for clinical trials.

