| Concomitant Medications /Therapi es | 1. No new medications are administered during the trial 2. However, they may be administered as needed at the discretion of the investigator. Participants will be excluded if they are taking any medications that, in the opinion of the investigator, may affect the endpoints of this study (e.g., antithrombotic agents (including antiplatelet agents and anticoagulants), psychotropic medications, antidepressant medications, medications related to hyperthyroidism, dietary supplements (red ginseng), OTC blood flow enhancers, medications that may affect tarsal tunnel, etc.) 3. Participants must not take any additional medications during the study period, including Example) Antithrombotic medications (including antiplatelet and anticoagulant medications), psychotropic medications, antidepressant medications, medications related to hyperthyroidism, dietary supplements (red ginseng), OTC blood flow enhancers, and medications that have the potential to affect tingling feet. |
| --- | --- |
| Methods | [figure not shown]  This study is a randomized, multicenter, parallel design, clinical trial. All participants in this study will be fully informed, signed informed consent, assigned a study box identification code, and randomized to one of three arms: no-treatment control, acupuncture treatment, or electroacupuncture treatment. Each participant will visit each study site 10 times, including a screening visit, randomization, and then twice a week for a total of 10 visits. This is a total of 12 visits including screening. The study duration is 5 weeks, with a follow-up visit 4 weeks after the end of the study. |
| Treatment adherence | Drop out if adherence to acupuncture treatment is less than 70% out of 10 visits. |
| Validation methods | 1. Primary outcome variable:   Visual Analog Scale (VAS) of coldhypersensitivity in the hands  Visual Analog Scale (VAS) of coldhypersensitivity in the feet   1. Secodary outcome variable:   (1) Body temperature: Thermometer measurement  (2) Pattern Identification Questionnaire, Coldness Diagnostic Questionnaire  (3) Quality of Life Questionnaire (WHOQOL-BREF) |
| Evaluation of safety | Vital Signs (at every visit), Hematology (WBC, RBC, Hemoglobin, platelet), Blood Biochemistry (BUN, Creatinine, AST, ALT, r-GTP) (at the end of trial)  Safety will be evaluated based on the results of the investigator's examination, adverse event monitoring, and clinicopathologic examination |

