##### C. Number of participants

1. Targeted number of participants

|  | Acupuncture  group | Electroacupuncture  group | No treatment group  (control group) | Total number of participants |
| --- | --- | --- | --- | --- |
| Number of eligible evaluations | 18 | 18 | 18 | 54 |
| Number of people considering a  25% dropout rate | 24 | 24 | 24 | 72 |

1. Calculation Rationale

This study was designed to test the hypothesis that acupuncture treatment of patients with coldhypersensitivity in the hands and feet will improve symptoms in the acupuncture treatment group and the electroacupuncture treatment group compared to the no-treatment control group.

The hypothesis of this study is below

H0 : σ = Δ1 – Δ2 = 0

H1 : σ = Δ1 – Δ2 ≠ 0

H0 : σ = Δ1 – Δ3 = 0

H1 : σ = Δ1 – Δ3 ≠ 0

Δ1: Mean change in VAS score from pre-treatment to post-treatment in acupuncture group

Mean change in VAS score of coldhypersensitivity in the hands and feet at week 10 (within ±3 days) after randomization in the acupuncture group

Δ2: Mean change in VAS score from pre- treatment to post-treatment in the electroacupuncture group

Mean change in VAS score of hand coldness at week 10 (within ±3 days) after randomization in the electroacupuncture group

Δ3: Mean change in VAS score from pre-treatment to post-treatment in untreated control group

Mean change in VAS score of hand coldness at week 10 (within ±3 days) after randomization in the no-treatment group

A clinical trial of coldhypersensitivity in the hands and feet with medical devices, acupuncture and electroacupuncture, are designed to estimate the number of participants based on the VAS information form the oxygen chamber device trial.

[figure not shown]
In the referenced trial by Ha et al., the mean VAS difference for the placebo group was -0.48 with a standard deviation of 1.03, and the mean VAS difference for the oxygen chamber group was -1.52 with a standard deviation of 1.17. The expected difference between acupuncture treatments for coldhypersensitivity in the hands and feet is 1.04, and the standard deviation is estimated to be 1.102 using the joint standard deviation formula.

Figure 1. Joint Standard Deviation Formula

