The significance level (α), the probabiiity of committing a TypeⅠerror, was set at 0.05, and the probability of committing a TypeⅡerror (β) was assumed to be 0.2. The number of participants in the electroacupuncture treatment group and the no-treatment control group was set to be the same, and the formula for estimating the number of participants by comparing the mean of the two groups was as follows.

[figure not shown]

N = [2*(1.96+0.84)^2*1.17^2]/(1.04)^2=17.625 ≒ 18

Based on the above, the number of participants is 18 in each arm. Considering a 25% dropout rate, 24 participants will be enrolled per arm.

18 ÷ (1-0.25) =24

Therefore, we plan to enroll 24 participants in each of the acupuncture treatment group, electroacupuncture treatment group, and no-treatment control group for a total of 72 participants to be analysed.

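### The 5% error and 80% power are set for one two-group test, but the protocol has two primary VAS scales, two or three arm contrasts and no rule saying which result decides

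*Protocol*

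**What the plan says.** **Primary variables.** The Clinical Protocol Overview lists the hand VAS and, on a separate line, the "Visual Analog Scale (VAS) of coldhypersensitivity in the feet". Section Primary outcome variable gives each its own line, anchors and score. No combined score is defined.

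**Hypotheses.** Section C. Number of participants writes two null hypotheses. One compares acupuncture with electroacupuncture. The other, "H0 : σ = Δ1 – Δ3 = 0", compares acupuncture with no treatment. The change is defined on hands and feet for the acupuncture arm but on hand coldness for the other two arms.

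**Analysis.** Section How to analyze validity variables tests no treatment against acupuncture or electroacupuncture, by repeated ANOVA, paired t-test and an open-ended remainder. The Overview adds ANOVA and words the comparison across all three groups. Under General principles, "the significance level is 0.05 by two-sided test".

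**Sample size.** Section C takes error probabilities of 0.05 (Type I) and 0.2 (Type II). It makes electroacupuncture and no treatment equal in size and rests on a single comparison: "the formula for estimating the number of participants by comparing the mean of the two groups was as follows". The assumed difference in VAS change is 1.04, borrowed from an oxygen chamber device trial. On the spread it says: "the standard deviation is estimated to be 1.102 using the joint standard deviation formula".

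**The concern.** Three parts of the protocol describe three different primary comparisons. The contrast that sizes the trial (electroacupuncture versus no treatment) is not a written hypothesis. The written contrast between the two treated arms is not among the no-treatment comparisons in the analysis section. The error and power figures belong to one test on one scale.

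The protocol does not say whether one scale or both must succeed, or on which contrast. If any result counts, the false-positive rate exceeds 5%. If both scales must succeed, power falls below the stated 80% at the planned evaluable number. The trial is open-label for participants, who complete the VAS themselves. Leaving the deciding result open allows the favourable one to be chosen after the data are seen.

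**Working it through.** **1. The plan's own figure.**
- Pooled SD from the cited trial's 1.03 and 1.17: √((1.03² + 1.17²)/2) = √1.2149 = 1.102.
- N = 2 × (1.96 + 0.84)² × 1.102² / 1.04² = 15.68 × 1.2144 / 1.0816 = 17.61, so 18 per arm. Then 18 / 0.75 = 24.
- The figure reproduces for one two-sided test at 0.05. The printed formula shows 1.17, which would give 19.84, so 20 per arm; the printed result fits 1.102.
- Power at 18 per arm is 80.8% by the normal formula and 78.5% by the t-test. The t-test figure is the fair comparator below.

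**2. Number of tests.** Two written contrasts × two scales = 4. Adding electroacupuncture versus no treatment gives 3 × 2 = 6. Independent tests would give 1 − 0.95⁴ = 18.5% and 1 − 0.95⁶ = 26.5%. These are too high, because the contrasts share arms and the scales share participants.

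**3. Simulation.** Three equal arms, two normal change scores with SD 1.102, 18 per arm, 40,000 trials per setting (simulation error at most about 0.25 points). The documents give no hand-feet correlation, so 0.3 to 0.9 is an assumption. The power rows assume a 1.04 benefit on both scales in both treated arms and refer to electroacupuncture versus no treatment.

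| Rule | 0.3 | 0.5 | 0.7 | 0.9 |
|---|---|---|---|---|
| Error, any of 4 unadjusted tests | 17.0% | 16.0% | 14.7% | 12.5% |
| Error, any of 6 unadjusted tests | 22.5% | 21.3% | 19.6% | 16.5% |
| Error, one three-arm ANOVA per scale, either counts | 9.5% | 9.4% | 8.5% | 7.1% |
| Power, both scales on one contrast, no gate | 65% | 67% | 69% | 73% |
| Power, both scales, three-arm gate on each | 58% | 60% | 63% | 68% |
| Power, hand-feet mean, three-arm gate | 91% | 86% | 81% | 76% |

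Over the whole correlation range from 0 to 1, large-sample simulation gives 17.3% down to 9.1% for 4 tests, 22.8% down to 12.2% for 6, and 9.7% down to 5.0% for the ANOVA per scale.

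**4. Two further checks.** If all 24 per arm are analysed, requiring both scales on one contrast gives 81-86% power. The gated mean score holds the error at about 5% when no arm differs.

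**The case against.** A reader might infer that every contrast on each scale is tested separately at 0.05, so that the trial's actual false-positive rate is 12-22%. The documents do not support that. The single 0.05 is not said to apply per contrast and per scale. No two-sample t-test is named for the primary VAS, and the paired t-test is assigned to change within a group. The Overview names ANOVA across three groups, which on each scale gives about 7-10%. The top of the range also needs all three contrasts and a low correlation that the protocol does not give. The 12-17% and 16-23% figures are therefore conditional on any unadjusted test counting as success.

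Pairwise adjustment and test order are also commonly left to an SAP, so their absence alone is no finding. That stands. What remains is a conflict inside the protocol: an SAP could add an adjustment, but it could not make the written hypotheses, the analysed contrasts and the sized contrast agree without changing one of them. Nor is the ANOVA fixed as a gate, since the list of methods is open-ended. Even as a gate it exceeds 5% across two scales unless they are perfectly correlated.

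A third objection also stands in part. Setting t-test power of 65-73% against a normal-formula 80% overstates the loss from requiring both scales. Against 78.5% it is about 5 to 14 points, and it applies at 18 evaluable per arm.

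**Conclusion.** The point holds as a mismatch. The stated 5% error and 80% power belong to one two-group test, while the protocol sets two primary scales, two written hypotheses that omit the sized contrast, and an analysis that brings in a third contrast. Which error or power applies depends on a success rule that the protocol does not state:

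- any unadjusted test counts: about 12-17% error with two contrasts, 16-23% with three;
- one three-arm ANOVA per scale: about 7-10% error;
- both scales required on one contrast: at most 5% error for that contrast, with about 65-73% power at 18 per arm.

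These ranges rest on an assumed correlation of 0.3 to 0.9 and normal change scores. The power figure also assumes equal effects of 1.04 on both scales.

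**What to change.** **Align the three parts.** Put electroacupuncture versus no treatment among the hypotheses, define the change on the same scale in every arm, and make the hypotheses, the sample-size contrast and the analysis name the same comparisons.

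**Fix one success rule.** Name a single primary VAS score. Test it with one three-arm test at two-sided 0.05. Only if that is significant, test the three pairwise contrasts, each at 0.05. With three arms this is a closed procedure and holds the family-wise error at 5%.

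**Choice of score.** The hand-feet mean is one option, with hands and feet reported separately as secondary. State its downside. Power for electroacupuncture versus no treatment at 18 per arm is about 76-91% if both regions improve equally in both treated arms, and about 70-87% if acupuncture has half the effect. It falls to about 21-32% if only one region improves. That last case is realistic, because the screening text admits a VAS of 4 or more in hands or feet.

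**If both scales stay primary.** Require both to succeed on the same contrast and apply the three-arm gate to each scale. Restate power at 18 per arm as about 58-68%, or 65-73% for one pre-named contrast without the gate. Without the gate, three contrasts give about 12% false both-scale claims when feet differ strongly across all arms and hands do not. Even with it, if the null is true for one contrast on hands and for another on feet, the bound is 0.05 + 0.05 = 0.10, so the single score or one pre-named contrast is cleaner.

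**Cost.** Protocol and SAP wording, with no extra participants needed to adopt the rule. A claim for hands alone or feet alone becomes secondary, a pairwise claim needs the three-arm test first, and the stated 80% must be replaced by the power of the rule chosen, which is below 80% in some of these settings.

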##### Compare baseline demographic and assessment variables

To test whether the distribution of variables in the treatment and control groups is homogeneous, analysis of variance (ANOVA) or nonparametric methods are used for continuous variables, and Chi-square test is used for categorical variables.

##### How to analyze validity variables

- - 1. Primary efficacy endpoint: Visual Analogue Scale (VAS) coldhypersensitivity in the hands and feet

The primary efficacy evaluation variables will be analyzed using the ITT group as the main analysis group, and the results of the PP group will be presented in addition. Repeated ANOVA, paired t-test, etc. will be performed to test whether there is a difference in the change in VAS score between the no-treatment control group and the acupuncture treatment group or the electroacupuncture treatment group. The comparison of the degree of improvement of VAS scores within each group will be performed by paired t-test using the difference between pre- and post- treatment VAS scores (VAS score at Weeks 5±3 days - VAS score at Visit 1).

- - 1. Secondary Validation Variables
       1. Body Temperature (BT; thermometer measurement): Repeated ANOVA is performed to test whether there is a difference in BT change between the acupuncture treatment group and the electroacupuncture treatment group. To compare the degree of improvement in BT within each group, a paired t-test will be performed using the difference between BT before and after acupuncture treatment (BT at Weeks 5±3 days - BT at Visit 1).
       2. WHOQOL-BREF Quality of Life Assessment Questionnaire: ANOVA and post hoc tests will be used to test the difference between each group. Comparison within each group is done by paired t-test using the difference in values before and after acupuncture treatment (value at Weeks 5±3 days - value at Visit 1).
       3. Pattern Identification Questionnaire:
          - This figure shows the distribution of the dialectical observables (dialectical indicators) in participants with coldhypersensitivity in the hands and feet. To determine the relationship between the dialectical indicators and the change in symptom VAS, an ANOVA test (non-parametric test if not normally distributed) and post hoc tests are performed for each indicator with the change in symptom VAS as the dependent variable.
          - Validity and reliability of the basic instrument are evaluated. The validity evaluation is

a. Construct validity: The construct validity is evaluated by conducting a factor analysis of the items of the basic dialectic tool. After obtaining the scores of each item of the basic argumentation tool, the correlation matrix between the items is obtained. Determine the number of factors by the eigen value of the factor, rotate the factor after checking the construct validity, and interpret and name the items with large factor loadings related to the rotated factor based on the content of the items. b. Predictive validity: Evaluate the correlation between the values of the visual analog scale and the scores of the factors explaining cold feet. It estimates the degree of correlation between the visual analogue scale values of participants with coldhypersensitivity in the hands and feet and the sum of the scores of items that can well explain coldhypersensitivity in the hands and feet. Cronbach's alpha was measured to evaluate the questionnaire. In addition, we will analyze the changes i n the items and the magnitude of each item before and after the treatment, and the magnitude of the treatment effect for each specific type of excuse. In addition, we will use cluster analysis or factor analysis to identify the association and excuse relevance of excuse items related to coldhypersensitivity in the hands and feet.

- - - 1. Coldness Diagnostic Questionnaire:
         - Cronbach's alpha is used to analyze reliability. We also use the statistical method of Item-Total Correlation to analyze the correlation between items by measuring the Pearson correlation coefficient between the total scores of the remaining items.
         - Perform additional cluster analysis and factor analysis.
      2. Quality of life assessment EQ-5D: The EQ-5D index score does not have an officially established cutoff value to assess impaired health-related quality of life, but it is utilized for economic evaluation using the 4th and 5th quintiles.

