##### Secondary purpose

##### The efficacy of the study will be further evaluated by comparing the changes in scores on the Visual Analog Scale of coldhypersensitivity in the hands and feet, body temperature (thermometer measurement), Quality of Life Assessment Questionnaire (WHOQOL-BREF), Quality of Life Assessment EQ-5D, pattern identification questionnaire, and coldness diagnostic questionnaire between the no-treatment control group, acupuncture treatment group, and electro-acupuncture treatment group.

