##### Score:

- 1. **Secondary outcome variable**
     1. Body temperature: Thermometer measurement
- The difference in temperature between the bilateral palm (PC8), arm (LU4), anterior thigh (ST32), and dorsum of foot (LR3) regions, measured within 10 minutes of each visit, before the start of treatment and after the end of treatment, respectively, using a thermometer

[figure not shown]

[figure not shown]

[References]

Lee MJ, et al. A clinical case study to evaluate the hot flush and abdominal cold hypersensitivity relief efficacy of Cheonglijagamtang in climacteric women by DITI. Journal of oriental medical thermology. 2010;8(1):26-32.

Kim EG, et al. A clinical case study for the diagnosis and assessment of abdominal cold hypersensitivity treatment by DITI. Journal of oriental medical thermology. 2009:7(1):55-65.

Cho JY, et al. A case report of cold hypersensitivity of hands and feet patient. The journal of oriental obstetrics & gynecology. 2011;24(3):195-202.

Lee YJ, et al. Effects of far-infrared rediating products on coldhypersensitivity of lower limbs using cold stress test (CST): a pilot study. Journal of oriental medical thermology. 2008;6(1):69-75.

- - 1. Quality of Life Assessment Questionnaire (WHOQOL-BREF) and Quality of Life Assessment EQ-5D
- Overall quality of life, general health, physical health, psychological health, social relationships, and environment, measured at visits 1, 10, and 11.
  - 1. Pattern Identification Questionnaire
- Pattern identification questionnaire measured at visit 1 to correlate symptoms and VAS changes in patients with cold feet according to dialectic indicators.
  - 1. Coldness Diagnostic Questionnaire
- Coldness Diagnostic Questionnaire, which asks participants about their subjective or objective symptoms of coldness, is measured at Visit 1, Visit 10, and Visit 11.

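### The EQ-5D quintile rule is undefined, gives no utility difference, and does not deliver the between-arm comparison of score change that the protocol promises

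*Protocol*

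**What the plan says.** The Protocol deals with EQ-5D in four places.

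- **Secondary purpose** makes it part of the efficacy evaluation, by "comparing the changes in scores on the Visual Analog Scale of coldhypersensitivity in the hands and feet" and on a list of further measures that ends with "Quality of Life Assessment EQ-5D, pattern identification questionnaire, and coldness diagnostic questionnaire between the no-treatment control group, acupuncture treatment group, and electro-acupuncture treatment group". The objective is therefore score change, compared between three arms.
- **Statistical Methods, General principles** sets the default for efficacy indicators: "The basic analysis method is the degree of change between the results of the baseline test performed before the clinical trial" and the end-of-trial test, two-sided at 0.05.
- **Secondary outcome variable** and both visit schedules place EQ-5D, with WHOQOL-BREF, at three time points in all arms: "social relationships, and environment, measured at visits 1, 10, and 11".
- **How to analyze validity variables** has the one EQ-5D-specific analysis sentence. It observes that the index "does not have an officially established cutoff value to assess impaired health-related quality of life", and continues that "it is utilized for economic evaluation using the 4th and 5th quintiles".

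The statistical summary in the Clinical Protocol Overview has no EQ-5D entry. For the companion measure, WHOQOL-BREF, the same analysis section names ANOVA with post hoc tests between arms and paired t-tests within arms.

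**The concern.** The sentence responds to the lack of an accepted threshold for impairment by turning to quintiles. A quintile taken from a sample says where a participant ranks in that sample. It does not say whether her quality of life is impaired, or by how much it has changed.

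The text also leaves open four things on which the meaning of the result depends: whose distribution defines the quintiles, at which visit, which end is the impaired end, and what is compared with what. Some of the available choices give an answer that is fixed before any data are collected.

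The stated use is economic evaluation. Quintile membership gives no difference in utility, and the protocol plans no cost data to set against one.

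At stake is whether an outcome measured three times in every arm is analysed in a way that answers the protocol's own secondary objective.

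**Working it through.** The plan gives no EQ-5D cut-off, proportion or power, so there is no figure to reproduce. The check asks what the split can show under each reading that the text allows.

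**Inputs from the protocol.** Quintiles 4 and 5, from How to analyze validity variables. Arm size, from Number of participants: "Considering a 25% dropout rate, 24 participants will be enrolled per arm", hence 72 in total. Measurement at Visits 1, 10 and 11.

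**Assumptions.** Standardised normal scores, correlation 0.6 between baseline and follow-up, true gains of 0.5 or 1.0 SD. None of these is a protocol figure for EQ-5D.

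**Step 1: the built-in share.** Two of five quintile groups hold 2/5 = 40% of the sample that defines them. In whole participants without ties, this is 29/72 = 40.3% for the pooled sample and 10/24 = 41.7% for one arm.

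**Step 2: share in quintiles 4-5 at follow-up** (simulation, 3,000 trials, three arms of 24; quintiles numbered upwards):

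| Quintiles defined by | Quantity | Gain 0.5 SD | Gain 1.0 SD |
|---|---|---|---|
| Each arm's own follow-up scores | Every arm | 41.7% | 41.7% |
| Pooled follow-up scores | Total, all 72 improve | 40.3% | 40.3% |
| Pooled follow-up scores | Needled arms v control, only needled arms improve | 46.5% v 27.8% | 51.9% v 17.1% |
| Pooled baseline scores, held fixed | Total, all 72 improve (40.3% at baseline) | 59.8% | 77.4% |
| Pooled baseline scores, held fixed | Needled arms v control, only needled arms improve | 60.2% v 40.4% | 77.3% v 40.2% |

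Hand check of the fixed cut-off: the 60th percentile of a standard normal is 0.253. After a 0.5 SD gain the share above it is P(Z > 0.253 - 0.5) = P(Z > -0.247), about 59.8%. After 1.0 SD it is P(Z > -0.747), about 77%.

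So the first two rows carry no information on improvement, and the last three do.

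**Step 3: information lost when arms can differ.** Take pooled quintiles at follow-up, control (24) against both needled arms together (48), and a 0.5 SD effect.

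- Continuous score: standard error = sqrt(1/24 + 1/48) = 0.25 SD, and 0.5/0.25 = 2.0. Approximate power is the normal probability below 2.0 - 1.96 = 0.04, about 52%. Simulation with a t-test (6,000 trials) gives 50%.
- Quintile split, chi-square test, same simulation: 28%.

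A separate run of 4,000 trials gave 51.3% and 27.5%.

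**Step 4: the split against the stated purposes.**

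- Secondary purpose asks for change in score between three arms. The split gives membership of a rank group, with no comparison named.
- General principles asks for change from baseline to end. The split is not tied to any visit.
- Economic evaluation needs a utility difference and, for a cost comparison, costs. The two visit schedules and the visit-by-visit procedures list no cost or resource-use item, and no economic objective or method appears elsewhere in the protocol.

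**The case against.** The best defence is that the sentence may not be an efficacy rule at all. It reads partly as a remark about the instrument, it links quintiles to economic evaluation, and the text around it is visibly affected by translation. Secondary purpose and General principles already commit the trial to comparing EQ-5D change, and nothing says that the quintiles replace this. The index is collected at three visits, so no analysis is prevented. Details such as the reference sample could be left to a statistical analysis plan, which is not shown. The stakes are low as well: the Overview does not list EQ-5D among the secondary outcomes, and WHOQOL-BREF also covers quality of life.

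Much of this stands, and it limits the point. It does not rescue the clause. The protocol is not silent here: it states a specific split for a specific use, and that split serves neither the stated use nor the stated objective.

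Several stronger conclusions are tempting, and the documents do not support them:

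- **That the rule cannot show improvement, or has zero power.** This holds only for own-arm quintiles or for the pooled total redrawn at each visit. The protocol does not choose those readings, and under the others the arms do differ.
- **That quintiles 4 and 5 are the healthiest participants, so the rule selects the wrong end.** This needs upward numbering, and no direction is stated.
- **That the power loss can be read at 0.94 SD.** That figure (1.04/1.102) is the planning effect for the coldness VAS, not for EQ-5D.
- **That ties at full health make the loss larger.** Nothing in the protocol says how common they would be. In a check with about 40% of controls at the ceiling, and tied scores placed in the upper group, power at 0.5 SD was 44% for the t-test and 37% for the split, against 49% and 28% without the ceiling. The loss shrank.

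**Conclusion.** The point holds in limited form. The one EQ-5D-specific analysis sentence leaves sample, visit, direction and comparison undefined. It puts a rank in place of a threshold, does not deliver the between-arm comparison of change promised elsewhere, and names an economic evaluation that the planned data cannot support.

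The size depends on the reading. The 40% identity is arithmetic, exact up to rounding and ties, but it makes the result uninformative only where the quintiles are redrawn on the group being classified and that group's total share is read. Where arms can differ, the cost is lost information, illustrated by 28% against 50% power. That illustration rests on normal scores, an assumed 0.5 SD effect, and a pooling of the two needled arms that the protocol does not specify, so it is not a forecast for this trial.

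The consequence is confined to one secondary outcome. The primary VAS analysis and the sample size are untouched. It still merits correction, because a better analysis is available from data already scheduled.

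**What to change.** 1. Delete the quintile clause from How to analyze validity variables.
2. In its place, analyse the EQ-5D index as a continuous score: change from Visit 1 to Visit 10 and to Visit 11, compared between the three arms, adjusted for the Visit 1 index and for site (the stratum named under Randomization Methods and Blinding), with 95% confidence intervals. This agrees with Secondary purpose and General principles.
3. Remove the reference to economic evaluation, or limit it to reporting the arm difference in the index over Visits 1, 10 and 11, for instance as an area under the curve. A full economic evaluation would need cost or resource-use data that are not now planned.

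Items 1 and 2, and either option in item 3, change wording only. EQ-5D is already scheduled in all three arms at these visits, so no new assessment or participant is needed.
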